### Study design

The research design for the evaluation of the orientation programme is a pre- and post-test, clustered staggered design with T1 (target *n* = 15) and T2 (target *n* = 15) groups. T1 will participate in the orientation programme initially, while T2 will participate in a subsequent orientation. The peer educator capacity of tuakana will be assessed at three stages: pre-intervention, post-intervention for the T1 group, and post-intervention of the T2 group. After the orientation programme, each tuakana will talk with each teina at least three times to address the specific life-transitions of teina. Teina also will complete three evaluations with variations for the two groups: (a) T1: pre-intervention, approximately four months post-intervention, and then four months after the second evaluation; (b) T2: pre-intervention, approximately four months after initial survey, and then four months post-intervention. This staggered approach was approved by the Board Advisory Group during the original proposal as fitting the mission of the organisation and the needs of kaumātua. Consistent with Kaupapa Māori principles, withholding an intervention from participants is not ethical. Thus, the research design enables a rigorous comparison of the orientation programme whilst ensuring that all teina receive the intervention. Further, the use of a staggered design is a strong, and pragmatic design for interventions in the health service sector [56]. Figure 1 illustrates the staggered research design. The project is registered with the Australia New Zealand Clinical Trial Registry (ACTRN12617001396314).

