### Sample and recruitment

Tuakana will be purposively sampled to include kaumātua with effective peer educator attributes. The advisory groups considered the relevant peer educator attributes for ageing research [41] and attributes within Te Ao Māori such as mana, pono, aroha and tika [6, 19]. Tuakana will receive koha (an offering) towards their participation in the programme, conversations with teina, and data collection over the duration of the project (approximately $45/event).

The project will have a target of 180 teina participants randomly selected from the RKCT client base of approximately 600 kaumātua that affiliate to various iwi (tribes). Tuakana will be removed from the sampling frame. Teina will be assigned to a tuakana with matched biological sex. The only exclusion criteria is ethnicity (i.e., not being Māori). Decline and retention rates (including reasons such as withdrawal and passing away) will be tracked. Teina will receive koha as a contribution towards their participation in conversations and data collection (approximately $40/event). Tuakana and teina will be assigned to T1 and T2 groups ideally using random assignment although convenience assignment will be accommodated and tracked (e.g., when they were able to participate or to match tuakana/teina).

The sample sizes of tuakana and teina were determined by a balance of resources and statistical power to determine the optimal design. We conducted power and sample size estimates based on the research design [57] and confirmed with the ‘od.exe’ software package [58]. The following assumptions were made: (a) probability value = .05; and (b) rho (intra-class correlation) = .10. Six teina for each tuakana results in power of .80 with a medium effect size (d = .55). A medium effect size was chosen given prior research on the impact of elder peer educators on self-rated health and related wellbeing outcomes [37, 38].

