### Measures

The measures included in this study centre on two core constructs: hauora (health) and mana motuhake (see Table 1 for a summary). Hauora is conceptualised using the whare tapa wha (four walls of a meeting house) model of health and wellbeing developed for Māori communities [59]. The model includes tinana (physical/body), hinengaro (mind/thought/intellect), whanaungatanga (social) and wairua (spiritual). Hauora is a necessary (although not sufficient) condition for achieving mana motuhake. Measures of these two supra-constructs include both quantitative and qualitative questions and will be part of both tuakana and teina surveys across the three-time periods. We will include demographic questions only at pre-intervention (e.g., ethnicity, age, relationship status, care of grandchildren, and who else lives with them). We also will include additional measures related to the intervention. The total number of questions were limited and short measures were used in awareness of response burden for kaumātaua.

**Table 1 Tab1:** Constructs and Measures

Construct	Measures	Number of Items
*Pre- and Post-Test Measures*		
Hauora—tinana/hinengaro	Self-rated health	1
Hauora—tinana/hinengaro	Health related quality of life—physical and mental wellbeing	7
Hauora-hinengaro	Knowledge and likelihood of using services	3
Hauora-wairua	Spirituality	1
Hauora-whanaungatanga	Loneliness	4
Hauora-whanaungatanga	Cultural connection	4
Hauora-whanaungatanga	Social support	4
Hauora-whanaungatanga	Perceived burden & benefit	4
Mana motuhake	Economic wellbeing	3
Mana motuhake	Perceived autonomy	3
Mana motuhake	Global life satisfaction	1
Demographics	Living situation	3
*Intervention Measures*		
Mana motuhake	Satisfaction with interaction	3
Mana motuhake	Sense of purpose	3
Mana motuhake	Self-efficacy as a tuakana	5
Mana motuhake	Perceived effectiveness of orientation programme	4

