#### Intervention evaluation

The purpose of the analysis is to determine whether the peer-educator model results in changes to hauora and mana motukahe between pre-test and post-test. The analysis will compare the two groups and identify if there are intervening variables that explain differential patterns in the changes in the dependent variables*.* The dependent variables are mana motuhake and haurora. The independent variables are the time receiving the orientation programme (T1/T2) and the three time periods (pre-intervention, post T1-intervention, post T2-intervention). Potential intervening variables that will be controlled for include characteristics about the conversations, characteristics of the tuakana/teina, and whether participants talked with each other during the intervention.

The quantitative data are at three levels—repeated measures of variables (three-time periods), individual characteristics of the teina/tuakana, and characteristics about the conversations with the tuakana. The inclusion of multiple levels requires the use of multilevel statistical models to account for clustering. The analysis will account for the nature of the change in the variables along with characteristics about the teina and tuakana that may influence those changes.

Further, we will determine estimates of cost effectiveness using incremental cost effectiveness analysis (ICEA) [75, 76]. Cost-effectiveness analysis involves estimating the cost per unit improvement in the primary outcome variable. We will use HRQOL as an outcome measure for the ICEA [77]. ICEA involves estimating the ratio of the increase in the outcome variable (as measured by the estimated effect size from the intervention trial) to the estimated average cost per participant of the programme (the incremental cost-effectiveness ratio, or ICER). This calculation assumes that the cost of the status quo (no intervention) is zero. ICER is a common measure used in the evaluation of cost-effectiveness of health interventions [78, 79]. The ICER can then be compared with an explicit target (or costs of alternatives) to determine cost effectiveness.

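### Same-sex matching makes sex a whole-cluster factor, yet T1/T2 assignment is not described as balanced by sex and sex is not named as a model term

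*Protocol article*

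**What the plan says.** All references are to the protocol article.

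- **Matching.** Sample and recruitment: "Teina will be assigned to a tuakana with matched biological sex". Sex is the only matching factor named there.
- **Clusters.** Study design describes a "clustered staggered design with T1 (target *n* = 15) and T2 (target *n* = 15) groups", so there are 30 tuakana. With a target of 180 teina, each has six.
- **Assignment.** Sample and recruitment: "Tuakana and teina will be assigned to T1 and T2 groups ideally using random assignment". The same sentence accepts convenience assignment, to be tracked, and gives matching of tuakana and teina as one example of when it may be used. Stratification or balancing by sex is not mentioned.
- **Power.** Sample and recruitment assumes a significance level of .05 and "rho (intra-class correlation) = .10", and concludes: "Six teina for each tuakana results in power of .80 with a medium effect size (d = .55"). It does not say whether the .10 includes variation due to sex.
- **Model.** Intervention evaluation: "Potential intervening variables that will be controlled for include characteristics about the conversations, characteristics of the tuakana/teina". It plans multilevel models that account for clustering, over three time periods, and is concerned with change from pre-test to post-test. Sex is neither named nor excluded.

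**The concern.** Once every teina has the sex of their tuakana, sex cannot vary within a cluster. Any sex difference in an outcome then adds to the variance between tuakana, which is the component that limits a clustered comparison. Any sex imbalance between T1 and T2 also arrives about six teina at a time.

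The assignment rule adds a second problem. If convenience assignment is used to make tuakana-teina pairs work, and pairs must be of one sex, the matching can itself decide who enters T1 and who enters T2. For example, tuakana of one sex might become available later and fall mostly into T2. That imbalance would be systematic, and tracking it would record it without preventing it.

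At stake is precision in the T1-T2 teina comparison and, if assignment does sort by sex, a difference between the sexes in how outcomes change being mixed with the programme effect.

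**Working it through.** **Inputs from the article:** 30 tuakana (15 + 15), 6 teina each, intra-class correlation .10, significance level .05 (taken as two-sided), d = .55, stated power .80.

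**Assumed, because the article gives neither:** a sex difference δ of .3 to .5 SD in the outcome, and a share p of 50% to 70% of tuakana being of one sex.

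**1. The plan's own power figure.** With total variance 1, the between-tuakana variance is .10 and the within-tuakana variance is .90.

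- Design effect = 1 + (6 − 1) × .10 = 1.5; effective size = 90 / 1.5 = 60 per group.
- SE = √(4 × (.10 + .90/6) / 30) = √(4 × .25 / 30) = .183.
- Noncentrality = .55 / .183 = 3.01. Power is .828 from a noncentral t with 28 df, or .854 from the normal approximation.

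The stated .80 is therefore slightly conservative. At d = .55 (t, 28 df), power falls below .80 once the intra-class correlation passes about .123.

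**2. Variance that sex adds between tuakana:** v = p(1 − p)δ².

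- δ = .3: .25 × .09 = .0225 (p = .5); .21 × .09 = .0189 (p = .7).
- δ = .5: .25 × .25 = .0625 (p = .5); .21 × .25 = .0525 (p = .7).

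**3. Power at d = .55 (t, 28 df) under the two readings of .10**

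| δ | p | v | .10 excludes sex, sex left out: SE = √(4(.25 + v)/30) | Power | .10 includes sex, sex adjusted: SE = √(4(.25 − v)/30) | Power |
|---|---|---|---|---|---|---|
| .3 | .5 | .0225 | .191 | .795 | .174 | .862 |
| .3 | .7 | .0189 | .189 | .801 | .175 | .856 |
| .5 | .5 | .0625 | .204 | .739 | .158 | .919 |
| .5 | .7 | .0525 | .201 | .753 | .162 | .905 |

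The reference value is .828 in both cases. The unadjusted figures hold d = .55 on the within-sex SD. If d is instead scaled to the larger total SD, the even-split values are .804 (δ = .3) and .765 (δ = .5). Spending one cluster-level df on sex (27 in place of 28) lowers the adjusted powers by only about .001.

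**4. Chance imbalance in sex share under unstratified random assignment, 15 v 15 clusters**

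- SD of the T1-T2 difference = √(p(1 − p) × (4/30) × (30/29)). This is .186 with 15 of 30 tuakana of one sex and .175 with 20 of 30.
- With 180 teina assigned singly, √(p(1 − p) × (4/180) × (180/179)) = .075 and .070. The clustered figure is about 2.5 times larger.
- With 15 of 30 tuakana of one sex, the hypergeometric chance of a gap of at least 3 clusters (18 teina, 20 points) is .47, and of at least 5 clusters (33 points) .14. With 20 of 30, a gap of at least 4 clusters has chance .25.

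**5. Shift in a purely unadjusted post-test contrast:** (gap / 15) × δ. A 3-cluster gap gives .06 to .10 SD for δ = .3 to .5; a 5-cluster gap gives .10 to .17 SD. This is not the analysis that the article plans, so these values are not an estimate of its bias.

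**The case against.** The strongest reply has four parts.

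- **Adjustment is open, not refused.** A reader might infer that sex is left out of the model. The article does not support that: it commits to controlling for characteristics of the tuakana and teina, and sex is plainly one. The demographics listed under Measures omit sex, but the list is illustrative and sex must be known for matching. The full covariate list may sit in a document not shown. This stands: sex is unnamed, not excluded.
- **A stable difference in level largely cancels.** A reader might infer that a chance excess of one sex would be taken for a programme effect of up to .17 SD. That figure belongs to an unadjusted post-test contrast, whereas the plan models change over three time periods. A constant sex difference in level would mostly drop out; a sex difference in change would not. This also stands.
- **Clustered standard errors already carry chance imbalance.** Under true random assignment, between-tuakana variance from sex is part of the cluster-level error, so error rates hold and the cost is efficiency. This stands for random assignment. It gives no protection where convenience assignment sorts by sex.
- **The power loss is conditional.** It needs a real sex difference, no adjustment, and a .10 that excludes sex. The article establishes none of these. A reader might infer that the stated power is wrong; it is not, since its own inputs give about .83.

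What survives is the design gap. A later covariate list can add sex to the model, but it cannot balance clusters already assigned.

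**Conclusion.** The concern holds as a point about assignment and precision. Three facts follow from the article itself: sex is constant within clusters, assignment is not described as balanced by sex, and the convenience provision lets matching influence group membership. The SD of about .18 in the sex-share gap rests on those facts plus the assumed sex split, to which it is not sensitive.

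The effect on power rests on assumptions that the article does not settle. At a sex difference of .3 SD, power stays at about .80 even if sex is ignored and the .10 excludes it; at .5 SD it is about .74-.77. If the .10 includes sex, nothing planned is lost, but adjustment would gain about 3 to 9 points. These figures treat δ as a difference in whatever outcome the planned d refers to; for an analysis of change, only a sex difference in change counts.

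Confounding is a possibility only if convenience assignment sorts by sex and the sexes change differently. The change is worth making because it is nearly free, not because the planned analysis is shown to be invalid.

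**What to change.** 1. In Sample and recruitment, state that tuakana are randomised to T1 or T2 separately within male and female tuakana. Teina then follow their same-sex tuakana, so matching is not itself a reason to choose a group.
2. In Intervention evaluation, name sex as a prespecified fixed cluster-level covariate in every teina model, kept whatever its p-value. Because the outcome is change, let sex also act on change (a sex-by-time term).
3. In the sample size paragraph, say whether the .10 is before or after accounting for sex.

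Same-sex matching stays as it is. The cost is two assignment lists in place of one and one cluster-level degree of freedom for sex, plus the time terms if the sex-by-time term is used. No new data are needed, since sex is already known from matching. If tuakana have already been assigned, the second and third changes still apply, and the number of male and female tuakana in each group should be reported.

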### Measures

The measures included in this study centre on two core constructs: hauora (health) and mana motuhake (see Table 1 for a summary). Hauora is conceptualised using the whare tapa wha (four walls of a meeting house) model of health and wellbeing developed for Māori communities [59]. The model includes tinana (physical/body), hinengaro (mind/thought/intellect), whanaungatanga (social) and wairua (spiritual). Hauora is a necessary (although not sufficient) condition for achieving mana motuhake. Measures of these two supra-constructs include both quantitative and qualitative questions and will be part of both tuakana and teina surveys across the three-time periods. We will include demographic questions only at pre-intervention (e.g., ethnicity, age, relationship status, care of grandchildren, and who else lives with them). We also will include additional measures related to the intervention. The total number of questions were limited and short measures were used in awareness of response burden for kaumātaua.

**Table 1 Tab1:** Constructs and Measures

Construct	Measures	Number of Items
*Pre- and Post-Test Measures*		
Hauora—tinana/hinengaro	Self-rated health	1
Hauora—tinana/hinengaro	Health related quality of life—physical and mental wellbeing	7
Hauora-hinengaro	Knowledge and likelihood of using services	3
Hauora-wairua	Spirituality	1
Hauora-whanaungatanga	Loneliness	4
Hauora-whanaungatanga	Cultural connection	4
Hauora-whanaungatanga	Social support	4
Hauora-whanaungatanga	Perceived burden & benefit	4
Mana motuhake	Economic wellbeing	3
Mana motuhake	Perceived autonomy	3
Mana motuhake	Global life satisfaction	1
Demographics	Living situation	3
*Intervention Measures*		
Mana motuhake	Satisfaction with interaction	3
Mana motuhake	Sense of purpose	3
Mana motuhake	Self-efficacy as a tuakana	5
Mana motuhake	Perceived effectiveness of orientation programme	4

### Hauora

For physical and mental health, we will include a single item for self-rated health [60, 61] and seven items adapted from the Medical Outcomes Study [62] as measures of health-related quality of life (HRQOL). These are well-established and valid approaches for measuring HRQOL although the adaption will result in a need to re-establish factorial validity. Also in reference to physical/mental health, we developed new questions related to knowledge of health and social services. These are primarily open-ended questions to explore participants’ understanding of health services related to life transitions. An additional file lists all questions created specifically for this study in English and Māori (see Additional file 1). For spirituality, we will include a single item that came from Te Kupenga (the Māori Social Survey run by Statistics New Zealand) focused on strength of spirituality [63].

For social health and wellbeing, we will include four different measures. Loneliness will be measured by three items from a study of older New Zealanders [1] and one item created for this study. Cultural connection to iwi and hapū (subtribe) will be measured by four items from a study of older Māori [16]. Social support will be measured by four items from a scale used in the study of older New Zealanders although the scaling was changed from dichotomous to ordinal [64]. Finally, perceived burden and benefit on the family will be measured by four items; two items on burden came from a study of self-perceived burden [65] and the two benefit items were created for this study. See Additional file 1 for items created for this study for the tuakana and teina questionnaires; see Additional file 2 for items created for this study for tuakana questionnaires only.

### Mana Motuhake

We will include three quantitative measures of mana motuhake and several open-ended questions for both tuakana and teina. Economic wellbeing focuses on needs related to paying bills, quality of housing, and control of resources. Two items come from Te Kupenga and one was created for this study [63]. Perceived autonomy examines the independence that kaumātaua self-reported and will be measured with two items from a previous study [66] and one item from Te Kupenga. Global life satisfaction will be measured using the Cantril ladder [67]. Finally, we will ask five open-ended questions about general life concerns, concerns in the next few years, best things in life, what would improve their lives and how they assess their own mana motuhake. For tuakana only, we also will ask questions about sense of purpose. Three self-reported items will be included based on a previous study [68].

### Intervention-related measures

Several measures of mana motuhake will be directly related to the intervention. Based on a guideline for creating self-efficacy scales, five items were created for this study to assess the perceived self-efficacy of tuakana in relation to their ability to fulfil the role of tuakana [69]. Using three items created for this study and one item from a previous study [70], the perceived effectiveness of the orientation programme will be determined by the tuakana. For both tuakana and teina, we will include three items created for this study about the perceived satisfaction of the interaction with each other in terms of the time spent, interaction, and advice provided.

Additional measures about the intervention will relate to the conversations between tuakana and teina. Tuakana will have at least three conversations with each teina over a two-three month period. Checklists will be provided to the tuakana to help structure their conversations with teina around specific aspects to be covered in the orientation programme. The conversations will be audio recorded with the permission of the participants. A research team member will code the conversations to check the fidelity of the conversations to the orientation programme. The coding sheet will be a similar checklist given to the tuakana. Coders will be trained by one of the senior research team members on the coding procedures and rules. A separate researcher will code approximately 10% of the interactions to establish inter-coder reliability prior to completion of the primary coding.

The intervention will enable participants to talk about their transitions and enhance meaning about them. There is a chance that T1 participants will talk with T2 participants in the other group; this is understandable and not something we wish to control. We will measure whether participants talk to other kaumātua at RKCT about the project/life transitions and used these measures as confounders in the analyses. These measures mitigate impact on research design.

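### As described, the contamination measure does not isolate untreated T2 members' contact with T1, so entering it as a confounder does not support the claim that it mitigates the impact on the design

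*Protocol article*

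**What the plan says.** The protocol article's section on intervention-related measures names the threat: "There is a chance that T1 participants will talk with T2 participants in the other group". It says the team does not wish to control this. It then states what will be recorded: "We will measure whether participants talk to other kaumātua at RKCT about the project/life transitions". It adds that the team "used these measures as confounders in the analyses" and concludes: "These measures mitigate impact on research design".

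The section on intervention evaluation returns to the variable as one of several potential intervening variables to be controlled for, now worded as "whether participants talked with each other during the intervention". That section also fixes the main model terms: "The independent variables are the time receiving the orientation programme (T1/T2) and the three time periods".

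Two further facts bear on the point. Teina are "randomly selected from the RKCT client base of approximately 600 kaumātua", so both groups come from one organisation. On item wording, the section on hauora says: "An additional file lists all questions created specifically for this study in English and Māori". That file is not part of the material at hand.

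**The concern.** Under the staggered design, T2 is untreated only until the second survey. T1 against T2 at that survey is the only concurrent comparison of treated with untreated people, and it is the comparison that cross-group talk shrinks. The harmful exposure is specific: a T2 member who has not started hears programme content from someone who has.

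The printed item is much wider than that exposure, and the second wording differs from it in partner, topic and analytic role. The protocol nevertheless relies on this variable alone to declare the problem dealt with.

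Two misreadings could follow. A high 'yes' rate made up mostly of ordinary conversation could be used to excuse a null result. A small yes/no difference within T2 could be taken as evidence of no contamination when it only reflects a non-specific item. Talk about the project also arises after assignment and may be a result of the programme, so treating it as a confounder is questionable in itself.

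**Working it through.** **1. The two wordings side by side**

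| | Intervention-related measures | Intervention evaluation |
|---|---|---|
| Partner | any RKCT kaumātua | participants |
| Topic | the project or life transitions | none stated |
| Partner's group | not stated | not stated |
| Role | confounder | intervening variable, controlled for |
| T2 still untreated at the time? | not stated | not stated |

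The respondent's own group and the survey round are known. The partner's status is missing from both.

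**2. How specific would a 'yes' be?** Inputs: 15 tuakana and a target of 180/2 = 90 teina per group, so 105 people each in T1 and T2, from about 600 clients. Assumptions: tuakana are counted among the 600, and conversation partners are random.
- Chance that one partner of a T2 member is in T1: 105/599 = .175. With one partner, about 82% of 'yes' answers to the wider item would not be cross-talk.
- Restricted to enrolled partners (105 T1 + 104 other T2): 105/209 = .502, so about half would not be.
- Any T1 contact among k partners, 1 − (1 − .175)^k: .175, .439 and .618 for k = 1, 3 and 5.

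**3. The plan's power.** With 15 clusters of 6 per group and ICC .10, the design effect is 1 + 5 × .10 = 1.5. At d = .55, two-sided α = .05 (sidedness is not stated), power is .854 (normal) or .828 (t, 28 df). If d is in within-cluster SD units it is .815 or .788. The stated .80 is therefore reproducible. No dilution allowance is among the listed assumptions.

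**4. Illustration of dilution.** Let y be the T2 'yes' rate, P the chance that a 'yes' includes T1 contact, and c the share of the effect carried over. Then observed d = .55 × (1 − c·y·P). Assume y = .60, k = 3, c = .5:
- truly exposed: .60 × .439 = .263 of T2;
- observed d = .55 × (1 − .5 × .263) = .478, with power .71 (t, 28 df);
- over y = .30 to .90 and k = 1 to 5, power runs from .81 to .56.

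**5. What the non-specific item would show.** The true exposed/unexposed difference within T2 is .5 × .55 = .275. The yes/no difference on the wide item is .275 × .439 = .12, with SE √(1/54 + 1/36) = .22, ignoring clustering.

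**6. Does adjusting for it remove the dilution?** In the same illustration, the T1-T2 contrast is .55 − .12 = .43 among those answering 'yes' and .55 among those answering 'no'. If 60% answer 'yes' in both groups and talk has no effect in T1, the adjusted contrast is .60 × .429 + .40 × .55 = .478, the same as unadjusted. Adjustment removes nothing.

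**7. Bounding instead.** If the exposed proportion is p and carry-over lies between 0 and 1, the undiluted d lies between d_obs and d_obs/(1 − p). With the specific proportion, p = .263: .478 to .478/.737 = .65. With every 'yes' counted as exposed, p = .60: .478 to .478/.40 = 1.19. At half carry-over the wide item would over-correct to .478/.70 = .68, against a true .55.

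**The case against.** A reader might infer that the trial has no means of measuring contamination. The documents do not support that. Group and time period are analysis variables, so T2 answers at the second survey can be separated. The items may be in the additional file, and the text speaks of measures in the plural, so project talk and life-transitions talk may already be separate questions. The wording in the section on intervention evaluation, read after the sentence about T1-T2 talk, may be shorthand for cross-group contact. These points stand and limit the finding to what the article prints. They do not remove it: if the second wording is shorthand for cross-group talk, it conflicts with the wider item, and the two still need reconciling.

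A reader might also say that, taken literally, every tuakana-teina pair answers 'yes' by design. That does not touch the group that matters, because T2 pairs have not begun their conversations before the second survey, and features of those conversations are listed separately.

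The power losses are caused by contamination, and a better item restores none of them. Random mixing is doubtful, since talk about the project probably concentrates among people in it; the 82% may be too high for such talk. Even a perfect item would have limited power: about 24 exposed against 66 unexposed T2 teina gives SE √(1/24 + 1/66) = .24, so .275 is only 1.15 standard errors. Finally, the repeated measures also allow T2's untreated interval to be compared with its treated one, so the T1-T2 contrast at the second survey is the only concurrent contrast, not the only one. All of this is fair. None of it supports the flat claim of mitigation.

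**Conclusion.** The point holds in a limited form. The article describes the contamination variable in two non-equivalent ways, and neither specifies contact between a not-yet-treated T2 member and a T1 member before the second survey. Entering such a variable as a confounder does not justify the statement that the impact on the design is mitigated, particularly as talk about the project arises after assignment. Even a specific item used as a covariate would in effect compare T1 with T2 members who chose not to talk, which assumes that talkers and non-talkers are otherwise alike.

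The documents give no contamination rate, mixing pattern or carry-over. The 17.5% rests on random mixing and on tuakana being among the 600 clients. The diluted d of .48 and the power range of .81 to .56 are illustrations under those and further assumptions, not losses that the fix recovers. What the fix improves is interpretation: in the illustration, the upper bound on the undiluted effect falls from 1.19 to .65. The change is worth making because it is nearly free and affects what can be concluded from a weak or null result.

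**What to change.** Reconcile the sections on intervention-related measures and intervention evaluation into one definition and one analytic role.

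- At the second survey, before T2 starts, ask T2 tuakana and teina whether they talked about the programme with someone already taking part in it.
- Record general talk about life transitions as a separate item. It need not be dropped, since some spillover may not be recognised by respondents as programme talk.
- Report the proportion of T2 answering 'yes', and use it in a sensitivity analysis that bounds dilution of the concurrent T1-T2 contrast over a stated range of carry-over. Do not use it as a covariate presumed to remove dilution.
- Replace the mitigation sentence with one saying that the measures describe possible dilution.

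First check the items in the additional file; if they already record the partner's status, only the article's wording and the analysis role need changing. Otherwise the cost is a reworded or split questionnaire item and a few sentences, with no added visit and negligible burden. The downside is recall error about who was already taking part.
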